#### Monocyte Isolation From Blood

Centrifuge the blood at 500 g for 10 min at room temperature. Then, the leucocyte-enriched layer on top of the RBC (red blood cell) pellet (buffy coat) will be diluted (1:4) with basal RPMI (Roswell Park Memorial Institute) media and applied to a Histopaque density gradient (specific gravity = 1.077/1.119, at room temperature, Sigma Chemical Co.) and centrifuged without application of the brake at 700 g for 30 min. then collect the peripheral blood mononuclear cells (PBMCs).

#### Bioenergetic Assessment of Monocytes

Determination of cellular bioenergetics will be performed after plating the cells on 8-well polystyrene plates designed for the extracellular flux (XF) analyzer (37). The number of PBMCs will be counted on Counstar automatic cell counter (IC 100, Shanghai Ruiyu Biotechnology Co.). Twenty microliter trypan blue will be added into the cell samples to get the number of living and dead cells, respectively. Researchers will resuspend purified monocytes and plate the diluted cells (300,000 living cells/well) in 200 μl on CellTak (BD Biosciences) coated assay plates and allow it to attach for 30 min at 37^°^C in a non-CO_2_ incubator. The cellular bioenergetics of the isolated cells will be determined using the XF analyzer (Seahorse Bioscience) in combination with the mitochondrial stress test (38). Real-time, non-invasive measurements of oxygen consumption rate (OCR) and extracellular acidification rate (ECAR) will be measured and correlated to mitochondrial function and glycolysis, respectively. The percent of non-mitochondrial and glycolytic monocyte OCR and ECAR will be assessed in the XF96 XF analyzer (Seahorse Bioscience) as a glucose stress test with sequential injections of glucose (5 mM), oligomycin (1.0 μg/ml) and 2-deoxyglucose (100 mM). Using the mitochondrial stress test protocol, inhibitors of the mitochondrial respiratory chain will be injected sequentially to assess the respiratory parameters: basal OCR, ATP-linked OCR, proton leak, maximal, and non-mitochondrial OCR. Reserve capacity will be calculated by the subtraction of basal OCR from maximal OCR. The optimum concentration of the inhibitors and activators to be used for the assessment of mitochondrial function were determined, as previously described (37, 39). The BHI was calculated using the following equation: (Reserve capacity × ATP-linked OCR)/(Proton leak × Non-mitochondrial OCR)^32^.

### Anesthesia and Surgical Procedure

All patients will undergo a standard preoperative assessment, including medical history, physical examination, laboratory blood tests, and a 12-lead ECG. If further investigations are necessary, they will be carried out at the discretion of the operating team. One day before surgery, responsible anesthetists will be asked to make a pre-operative subjective assessment of patients. Comorbidities are based on the medical history and self-reporting. Hypertension is considered to be present if the patient had previous medical documentation of hypertension and is currently taking antihypertensive medication. Coronary artery disease is defined as a history of angina; myocardial infarction; positive exercise, a nuclear or echocardiographic stress test; resting wall motion abnormalities on echocardiogram; coronary angiography with evidence of ≥ 50% vessel stenosis; or an electrocardiogram with pathologic Q-waves in 2 contiguous leads. A requirement for insulin or oral hypoglycemic therapy at the time of admission for surgery is considered to be diabetes mellitus. Arrhythmias are considered to be any type of previously diagnosed arrhythmias or abnormal ECG after admission. A patient will be considered a smoker, if they had a history of smoking within 1 year before surgery. Chronic obstructive pulmonary disease (COPD) was extracted from the patient’s primary care records and past medical history. Cerebrovascular disease was defined as a previous cerebrovascular accident or transient ischemic attack.

On the operation day, standard monitoring of electrocardiogram, pulse oximetry, non-invasive blood pressure and the bispectral index (BIS, Covidien LLC, MA, United States) will be performed throughout anesthesia to detect clinical vital signs. General anesthesia will be induced by intravenous propofol 1.5–2.5 mg/kg, and sufentanil 3 μg/kg, cisatracurium 0.2 mg/kg or vecuronium bromide 0.1 mg/kg subsequently administered. Anesthesia will be maintained with an intravenous remifentanil infusion and sevoflurane or desflurane inhalation or propofol TCI. After the surgery, patients will be transferred to the post-anesthesia care unit (PACU) or ICU.

### Outcome Measures

#### Primary Outcome

Trained members of the research team will assess patients for delirium use the Confusion Assessment Method (CAM) (40) or the Confusion Assessment Method for the Intensive Care Unit (CAM-ICU) (41) for patients who are unable to speak (e.g., still intubated) in the ICU. These methods (CAM and the CAM-ICU) are reliable and have been consistent with the Diagnostic and Statistical Manual of Mental Disorders, 4th edition diagnostic criteria for delirium (42). The severity of delirium will be assessed by the maximum daily score of the CAM-S, a severity scale for patients who screen positive for delirium based on the CAM.

Before the surgery, investigators will identify suitable patients and approach them by telephone between 1 day and 1 week before surgery. Those who consented will be performed delirium assessments 1 day before surgery. After the surgery, delirium assessments were done when patients could be aroused sufficiently (Richmond Agitation and Sedation Score –3 or higher) (43). Investigators will assess delirium twice per day from the first to the third postoperative day in the morning and afternoon. The new onset of delirium after the third postoperative day will be assumed to be unrelated to anesthetic or other intraoperative factors.

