## Introduction

### Background

Postoperative delirium (POD) is a cognitive disturbance characterized by acute and fluctuating impairment in attention and awareness. It commonly occurs between postoperative days 2–5. In the general surgical population, the incidence of postoperative delirium is reported to be 2.5–3% (1, 2). In patients aged more than 60–70 years, the incidence of postoperative delirium is considerably higher at 10–20% (3–5). Advancing age with decreased reserve and changes to the physical characteristics of the brain, including cerebral atrophy and changes in white matter, was associated with an increased risk of developing delirium (6–8). The severity of POD varies from individual to individual. Cognitive function changes may last for a few days, months or years, and there is a possibility of further deterioration (9). The occurrence of postoperative delirium lengthens hospital stay by 2–3 days and ICU stay by 2 days (10–12). Postoperative delirium is also associated with a 30-day mortality of 7–10%, compared with 1% in those without delirium (11–13).

Early identification of patients at high risk for delirium before surgery aids the clinician and allows for the development of strategies targeted at minimizing the occurrence of delirium. However, the multifactorial occurrence of POD makes it hard to foresee delirium even in fields with high incidence like cardiac surgery (14), and the tools for the prediction of delirium have shown to be insufficient (15). Potential blood markers can be divided into two categories: proinflammatory proteins and neuronal cell damage markers. Proinflammatory proteins are highly sensitive while with low specificity for the diagnosis or prediction of delirium, including IL-1, IL-6, C-reactive protein (CRP), interleukin, procalcitonin (PCT), and TNFa (16). Neuronal cell damage markers like protein S-100 and neuronal specific enolase (NSE) can only indicate an already ongoing detrimental process without any predictive ability. Beside blood markers, numerous risk prediction models are available for predicting delirium, including Katznelson, the original PRE-DELIRIC, and the international recalibrated PRE-DELIRIC model (13, 15, 17). But these models were formulated based on identified risk factors for patients in ICU (17). Validated prediction model for surgical patients is still lacking. All these limitations point to the need for better alternatives to assess preoperative risk of POD.

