### Hypothesis and Objectives

We hypothesis that poor mitochondrial function with aging process makes brain vulnerable to systemic inflammation by surgeries. As BHI of monocytes in peripheral blood can reflect brain mitochondrial function and surgical systemic oxidative stress, we assume patients with low BHI have higher risk of POD.

The main objective of the current study was to find whether HBI of monocytes isolated from individual’s peripheral blood (preoperative or postoperative) can predict delirium after major non-cardiac surgery in elderly patients during hospitalization. The secondary objective was to determine whether BHI can predict moderate or severe complications within 30 days after surgery, because these events are also associated with perioperative inflammation/oxidative stress and poor organ function.

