### Sample Size and Statistical Analysis

The sample size calculation was based on comparing the area under the curve (AUC) of the receiver operating characteristic (ROC) curves using MedCalc (Version 19). Assuming an outcome event rate of 9–11% (based on our previous study), a moderately good AUC of 0.8 for the BHI, a sample size of 112 patients had 90% power to detect this clinically relevant difference in AUC values (2-sided alpha of 0.05). To account for 10% of patients who may have been lost to follow-up, we aimed to recruit a total of 124 patients to the study. When the study finished, the missing data will be excluded.

Statistical analysis was performed using SPSS Version 15 software (SPSS, Chicago, IL, US). All statistical tests were 2 sided and significance was assumed at *P* < 0.05. Comparison of interval data was performed using independent sample *t*-tests, Mann–Whitney or Kruskal–Wallis tests when appropriate. The ROC curve analysis was performed to identify the predictive values of the BHI for POD and postoperative complications. The performance of continuous variables was analyzed with ROC curves, with the area under the curve (AUC) being calculated. Cutoff values were evaluated based on the Youden index. Relative risk (RR) and 95% confidence intervals (CIs) were estimated using a chi-squared test.

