In conclusion, our study will analysis correlations between HBI of monocytes isolated from individual’s peripheral blood and delirium after major abdominal surgery in elderly patients during hospitalization. By exploring new and more effective methods to predict POD, we hope to identify high risk patients before surgery and develop perioperative strategies for them. Also, this project will advance the use of clinical study mitochondrial function during surgery.

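### Delirium is assessed only on postoperative days 1–3, but the objective and conclusion are about delirium during the hospital stay

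*Protocol article*

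**What the plan says.** All places are in the protocol article.

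- **Hypothesis and Objectives.** The main objective is to find out whether the Bioenergetic Health Index (BHI) "can predict delirium after major non-cardiac surgery in elderly patients during hospitalization".
- **Discussion, closing paragraph.** The conclusion keeps that target: "delirium after major abdominal surgery in elderly patients during hospitalization".
- **Background.** On the timing of postoperative delirium: "It commonly occurs between postoperative days 2–5".
- **Primary Outcome.** The schedule is "Investigators will assess delirium twice per day from the first to the third postoperative day in the morning and afternoon". The next sentence deals with later onset: "The new onset of delirium after the third postoperative day will be assumed to be unrelated to anesthetic or other intraoperative factors".
- **Secondary Outcome.** Team members record other complications during the stay, in addition to the delirium assessments. This adds no delirium assessment after day 3.
- **Sample Size and Statistical Analysis.** "Assuming an outcome event rate of 9–11% (based on our previous study"), with "a moderately good AUC of 0.8 for the BHI", 112 patients give 90% power at two-sided alpha 0.05. The section does not say which postoperative window the event rate covers.

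**The concern.** The document uses three windows for one outcome: the hospital stay (objective and conclusion), days 2–5 (when delirium is said to be common) and days 1–3 (when it is measured). Days 4 and 5 are two of the four days the Background names, and no delirium assessment is planned on them.

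The sentence that sets later onset aside is an assumption given without evidence, and it speaks of anaesthetic and intraoperative causes. The study compares no anaesthetic exposures. It tests a marker of patient susceptibility, on the idea that "poor mitochondrial function with aging process makes brain vulnerable to systemic inflammation by surgeries". Delirium on day 4 or 5 in a patient with low BHI is not obviously outside that idea.

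What is at stake is mainly what the trial may conclude: a result on days 1–3 would be reported as a result on in-hospital delirium. A second, conditional risk is fewer events than planned, in a design that rests on about ten.

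**Working it through.** **1. Inputs.** From Sample Size and Statistical Analysis: n = 112, event rate 9–11%, AUC A = 0.80, two-sided alpha 0.05, power 90%. Assumed because not stated: a null AUC of 0.5, and a share f of delirium onsets that fall after day 3 (10% to 40%).

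**2. Reproducing the plan's figure.** The Hanley–McNeil variance with n1 cases and n0 non-cases is

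V(A) = [A(1−A) + (n1−1)(Q1−A²) + (n0−1)(Q2−A²)] / (n1·n0), where Q1 = A/(2−A) and Q2 = 2A²/(1+A).

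Power = Φ{[A − 0.5 − 1.96·√V(0.5)] / √V(A)}.

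At 9%, n1 = 112 × 0.09 = 10.08 and n0 = 101.92. Then √V(0.5) = 0.0957 and √V(0.8) = 0.0859, so (0.30 − 1.96 × 0.0957)/0.0859 = 1.31 and power is 90.5%. Solving for whole numbers of cases at 9% gives 10 cases + 102 non-cases = 112, exactly the stated size. At 11%, power at n = 112 is 95.0%. The plan therefore rests on about 10 delirium cases.

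**3. If the 9–11% rate covers the whole stay.** Suppose that late cases are counted as non-cases and that BHI predicts early and late onset equally well. For event rate p:

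- counted cases n1 = 112·p·(1−f)
- late cases m = 112·p·f
- counted non-cases n0 = 112 − n1
- observed AUC = 0.80 − 0.30·m/n0, because a late case compared with an early case has AUC 0.5.

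Example with p = 9% and f = 30%: n1 = 7.06, m = 3.02, n0 = 104.94. The observed AUC is 0.80 − 0.30 × 0.0288 = 0.791. The standard errors are 0.1128 (null) and 0.1034, so (0.291 − 1.96 × 0.1128)/0.1034 = 0.68 and power is 75.2%.

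| Share after day 3 (f) | 9%: cases / AUC / power | 11%: cases / AUC / power |
|---|---|---|
| 0 | 10.1 / 0.800 / 90.5% | 12.3 / 0.800 / 95.0% |
| 10% | 9.1 / 0.797 / 86.5% | 11.1 / 0.796 / 92.1% |
| 20% | 8.1 / 0.794 / 81.5% | 9.9 / 0.793 / 88.0% |
| 30% | 7.1 / 0.791 / 75.2% | 8.6 / 0.789 / 82.5% |
| 40% | 6.0 / 0.789 / 67.6% | 7.4 / 0.786 / 75.3% |

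**4. Does the coding of late cases matter?** If they were all identified and excluded (n0 = 101.92, AUC 0.80), power at 9% would be 87.3%, 83.2%, 78.0% and 71.4% for f = 10%, 20%, 30% and 40%. Lost events drive the loss; misclassified controls add little.

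**5. If the 9–11% rate is a days 1–3 rate.** The planned events are then the events that will be counted, and the row f = 0 applies. No power is lost, and the mismatch with the objective is unchanged.

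**The case against.** Several points on the other side have weight.

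- **Coding.** A reader might infer that true cases will be filed as controls. The text does not say so: a late case could be a non-case, excluded or reported separately, and a condensed article may leave this to a fuller document. This stands. The default is nevertheless clear enough to need a rule, because such a patient has only negative assessments, and onset that nobody looks for cannot be excluded reliably.
- **AUC.** A reader might infer material bias in the AUC. Within the range above the shift is at most about 0.014, so this is not a main harm.
- **Power.** A reader might infer that the trial is underpowered. That needs the event rate to cover more than days 1–3, and the previous study is not described. The late share is also an assumption. At an 11% rate with 10% late onset, power is still 92.1%, above plan.
- **Half the cases missed.** Days 4–5 are half of the days 2–5 span by count, but the documents do not say how onsets are spread over it. Delirium that begins by day 3 and persists is captured.
- **Rationale.** The sentence covers other intraoperative factors as well as anaesthetic ones, and surgery is itself intraoperative. An early window is thus an arguable choice for a hypothesis about surgical inflammation. This stands as a defence of measuring days 1–3. It does not justify describing the result as delirium during the hospital stay.

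**Conclusion.** The mismatch is explicit and nothing else in the document repairs it. Measured as planned, the primary outcome is delirium on postoperative days 1–3, and the trial cannot support its stated objective and conclusion about in-hospital delirium. This part rests on no assumption.

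The numerical consequences are conditional. The AUC bias is small (0.80 to about 0.79). If, and only if, the 9–11% rate covers the whole stay, a late share of 10–40% lowers power at n = 112 from 90% to 86.5–67.6% at the 9% rate, or from 95% to 92.1–75.3% at the 11% rate. These figures also assume a null AUC of 0.5 and equal prediction of early and late onset. The firm claim is that the windows disagree, not that the sample is too small. Severity: should be fixed.

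**What to change.** Make the windows agree, in one of two ways.

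1. **Restate.** Define the primary outcome, objective and conclusion as delirium within 3 days after surgery. Keep patients with later onset as non-cases, which they are for that outcome, and report any recorded late delirium separately. They should not be dropped from the controls: late delirium would be found only incidentally once assessment stops, and selecting controls on it could inflate the AUC. Cost: wording only.
2. **Extend, where still feasible.** Have the existing team continue the CAM/CAM-ICU assessments to discharge, which matches the present objective. Alternatively, continue to day 5 and reword the objective to delirium within 5 days; stopping at day 5 without rewording would leave the mismatch for longer stays. Report days 1–3 as a sensitivity analysis. Cost: a few short bedside assessments per patient still in hospital. Trial Design places enrolment in July–December 2021 and the article appeared in April 2022, so this route may already be closed.

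In both cases, state the window to which the 9–11% event rate refers, and if it is longer than the assessed window, redo the sample size with the matching rate. Also remove the sentence on onset after day 3 as a reason for setting late cases aside, and say plainly how they are analysed.

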#### Secondary Outcome

Besides delirium assessments, other complications after surgery will also be recorded by trained members during hospitalization. After discharge, patients will be contacted by telephone 30 days after surgery to confirm the incidence of post-discharge complications. The severity of complications will be categorized as mild, moderate, severe or fatal using a modified Clavien-Dindo Classification (CDC) scheme.

### Sample Size and Statistical Analysis

The sample size calculation was based on comparing the area under the curve (AUC) of the receiver operating characteristic (ROC) curves using MedCalc (Version 19). Assuming an outcome event rate of 9–11% (based on our previous study), a moderately good AUC of 0.8 for the BHI, a sample size of 112 patients had 90% power to detect this clinically relevant difference in AUC values (2-sided alpha of 0.05). To account for 10% of patients who may have been lost to follow-up, we aimed to recruit a total of 124 patients to the study. When the study finished, the missing data will be excluded.

Statistical analysis was performed using SPSS Version 15 software (SPSS, Chicago, IL, US). All statistical tests were 2 sided and significance was assumed at *P* < 0.05. Comparison of interval data was performed using independent sample *t*-tests, Mann–Whitney or Kruskal–Wallis tests when appropriate. The ROC curve analysis was performed to identify the predictive values of the BHI for POD and postoperative complications. The performance of continuous variables was analyzed with ROC curves, with the area under the curve (AUC) being calculated. Cutoff values were evaluated based on the Youden index. Relative risk (RR) and 95% confidence intervals (CIs) were estimated using a chi-squared test.

### Adverse Events and Serious Adverse Events

This is a prospective observational clinical trial and the only intervention on patients is vein puncture for blood collection. All drugs administered during anesthesia and surgery are based on usual clinical practice. Adverse events will be recorded and followed if they are found to be serious or/and related to the vein puncture during blood collection. The occurrence of this kind of adverse events will be monitored. The rest of the adverse events will be treated as they are during the normal clinical practice.

### Patient and Public Involvement

Our interest in this area arose from the need for a new method to enhance risk stratification before surgery and guide intraoperative and early postoperative management of elderly patients. Parents will not play a role in recruitment. Participants will be sent a lay summary of the results when they are published. As a prospective observational cohort study, there was no intervention in our study design and exerted no additional burden on patients. But participants were given an opportunity to comment on the study in the final questionnaire.

### Dissemination

Dissemination of the findings will apply to local, national and international levels. Main results of the trial concerning clinical effectiveness will be submitted to a leading medical journal. Additional results of exploratory statistical analyses and qualitative/mixed-methods analyses of process data will be published in specialized international journals. Beyond journal publications, we will disseminate results through presentations at national and international conferences.

## Discussion

POD is a common complication in older surgical population with significant sequelae and associated burden on healthcare. Management of it can be categorized into risk stratification, risk reduction, early diagnosis, and treatment. With appropriate risk stratification, POD could then be managed through risk reduction measures and prophylactic interventions; it would also be possible to monitor high risk patients more closely and implement treatments more promptly. However, the multifactorial manner of this syndrome has made it hard to predict it. Because of the shortage of current risk prediction models and blood markers, we are trying to find new ways based on mitochondrial function.

In fact, mitochondrial function has been implicated and studied in numerous complex age-related diseases, including AD, diabetes, and atherosclerosis. And people have tried to expand clinical application of mitochondrial theory based on these findings. For example, resveratrol, an activator of NAD (+)-dependent deacetylase enzymes, has been shown to have beneficial effects on glucose metabolism and vascular function in animal models and patients (44, 45). In the perioperative period, there is few studies about mitochondrial function. Although BHI of monocytes has been proved to be a sensitive measure of oxidative stress in human and significantly depressed in patients undergoing cardiac surgery (35.36), there is still no clinical study connect it with the postoperative complications. Considering the pathophysiology of POD in aging patients, inflammation and oxidative stress act as the common root cause. This is likely the first study to find whether perioperative mitochondrial function of monocytes isolated from an individual’s blood can predict POD. There are some limitations to this protocol. Firstly, in order to ensure patient safety, patients with hemodynamic instability will be withdrawn from the study, that might cause a potential selection bias. Then, rarely, monocytes isolated from blood samples may not be sufficient for bioenergetic assessment. These patients will be excluded from analysis and the missing data will cause an exclusive bias. Thirdly, this is a single center study and the sample size is relatively small.

In conclusion, our study will analysis correlations between HBI of monocytes isolated from individual’s peripheral blood and delirium after major abdominal surgery in elderly patients during hospitalization. By exploring new and more effective methods to predict POD, we hope to identify high risk patients before surgery and develop perioperative strategies for them. Also, this project will advance the use of clinical study mitochondrial function during surgery.

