### Recruitment of Patients and Blinding

The patients will be recruited from the department of surgical ward in West China Hospital of Sichuan University. Patients undergoing major abdominal surgery under general anesthesia will be included in the study after obtaining informed consent. Before the surgery, investigators will identify suitable patients and approach them by telephone between 1 day and 1 week before surgery. Informed consents will be provided and interpreted by trained investigators, and they will be informed that their peripheral blood samples will be taken in this study. Once participants signed the consents, they will be enrolled and anonymized by an identification code. The subjects can voluntarily withdraw from the trial at any time. The BHI tests will be carried out by a skilled investigator. Preoperative delirium assessment and postoperative follow-up will be performed by trained members of the research team respectively, and they will be blinded to the outcomes of each other. Patients will be free to withdraw from the study at any time for any reason without prejudice to future care, and with no obligation to provide the reason for withdrawal.

***Inclusion criteria:*** (1) patients aged over 65 years, (2) no limitation of gender, (3) American Society of Anesthesiologists (ASA) physical status I–III, (4) mentally competent, (5) Informed and written consent.

***Exclusion criteria:*** (1) known hematological diseases, (2) long term use of sedative or psychotropic drugs, (3) unstable mental state, (4) history of allergy to anesthetics, (5) with learning difficulties, or mentally handicapped, (6) hemodynamic instability, (7) organ transplant surgery.

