### The Bioenergetic Health Index Test

#### Blood Collection

All patients will undergo venous blood sampling twice to measure BHI (1–2 tubes, 5 ml/tube): before the surgery in the operating room and 1 day after surgery in wards. Blood was collected in vacutainers (BD Biosciences) containing 1.5 ml of ACD (acid citrate dextrose) solution (trisodium citrate, 22.0 g/l; citric acid, 8.0 g/l and dextrose 24.5 g/l). Blood samples need to be preserved temporarily at 4^°^C and send to the laboratory within 30 min.

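### Withdrawing unstable patients and naming only wards for the day-1 draw could make loss depend on illness; the exclusion and withdrawal rules need reconciling

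*Protocol article*

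**What the plan says.** Four parts of the protocol article bear on this.

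- **Instability.** Recruitment of Patients and Blinding includes it in the exclusion list ("6) hemodynamic instability, (7) organ transplant surgery") with no time point. The Discussion, under limitations, says that "in order to ensure patient safety, patients with hemodynamic instability will be withdrawn from the study, that might cause a potential selection bias". Adverse Events and Serious Adverse Events states that "the only intervention on patients is vein puncture for blood collection".
- **Place of sampling.** Blood Collection says that every patient is sampled twice, "before the surgery in the operating room and 1 day after surgery in wards". The Abstract also names wards for the second sample.
- **ICU patients.** Anesthesia and Surgical Procedure says that after surgery "patients will be transferred to the post-anesthesia care unit (PACU) or ICU". Primary Outcome provides CAM-ICU "for patients who are unable to speak (e.g., still intubated) in the ICU".
- **Missing data.** Sample Size and Statistical Analysis says: "When the study finished, the missing data will be excluded". The Discussion adds that the rare patients with too few monocytes are left out of the analysis, and concedes a bias from this.

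The main objective, under Hypothesis and Objectives, covers both preoperative and postoperative BHI as predictors of delirium.

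**The concern.** Screening out unstable patients before enrolment narrows the population to which the result applies. Withdrawing them after enrolment is different: it removes people from a defined cohort because of how ill they became. The protocol uses both words and does not say which rule operates. Nor does the safety reason reach as far as withdrawal. It could justify skipping a venepuncture, but not stopping bedside delirium assessment or the 30-day telephone call.

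The sampling text adds a second possible route. A patient still in ICU on day 1 can have a delirium outcome through CAM-ICU, but the protocol names no place other than a ward for that patient's second sample. If the draw is missed, the missing-data sentence takes over. This gap is not among the stated limitations.

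The study rests on about 10 delirium events. Under its own hypothesis, low BHI and surgical inflammation or oxidative stress raise delirium risk, so loss that follows illness could be related to both predictor and outcome. At stake are the reported incidence, the AUC, the Youden cutoff and, to a lesser degree, power.

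**Working it through.** **1. The plan's own figure.** Inputs from Sample Size and Statistical Analysis: AUC 0.8, event rate 9–11%, two-sided alpha 0.05, power 90%, 112 evaluable, 10% loss, 124 recruited. The null AUC is not stated; 0.5 is assumed.

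Hanley–McNeil variance for AUC A with n1 events and n0 non-events:

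Var(A) = [A(1−A) + (n1−1)(a−A²) + (n0−1)(b−A²)] / (n1·n0), where a = A/(2−A) and b = 2A²/(1+A).

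Power = Φ{[(0.8−0.5) − 1.96·SE(0.5)] / SE(0.8)}.

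At 9%, take n1 = 10 and n0 = 102. Then SE(0.5) = 0.0961 and SE(0.8) = 0.0862, so the argument is (0.30 − 1.96×0.0961)/0.0862 = 1.295 and power is 90.2%. This reproduces 112. For recruitment, 112/0.9 = 124.4 and 112×1.1 = 123.2, so 124 is consistent. The sample size is not in error.

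**2. Illness-related loss within the planned allowance.** Assumptions: 12 of 124 patients are lost, and their delirium risk is RR times that of the 112 retained. For overall risk r:

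- retained risk p = 124r/(112 + 12·RR)
- events kept = 112p
- events lost = 12·RR·p
- excess loss = events lost − 12r, because random loss of 12 patients already removes 12r events.

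For example, with r = 9% and RR = 3: p = 11.16/148 = 7.5%, kept 8.4, lost 2.7, excess 2.7 − 1.1 = 1.6.

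| r | RR | Retained risk | Events kept | Events lost | Excess over random | Power |
|---|---|---|---|---|---|---|
| 9% | 1 | 9.0% | 10.1 | 1.1 | 0 | 90% |
| 9% | 2 | 8.2% | 9.2 | 2.0 | 0.9 | 88% |
| 9% | 3 | 7.5% | 8.4 | 2.7 | 1.6 | 85% |
| 10% | 1 | 10.0% | 11.2 | 1.2 | 0 | 93% |
| 10% | 2 | 9.1% | 10.2 | 2.2 | 1.0 | 91% |
| 10% | 3 | 8.4% | 9.4 | 3.0 | 1.8 | 88% |
| 11% | 1 | 11.0% | 12.3 | 1.3 | 0 | 95% |
| 11% | 2 | 10.0% | 11.2 | 2.4 | 1.1 | 93% |
| 11% | 3 | 9.2% | 10.3 | 3.3 | 2.0 | 91% |

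The gross loss of 2.0–3.3 events should not be set against the planned 10, because those 10 already allow for 10% dropout. The relevant figure is the excess, 0.9–2.0.

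**3. Effect on the AUC.** An illustrative simulation used a true AUC of 0.80, a 10% event rate and 10% total loss, with loss following a logistic model (log-odds 1.1 for delirium; 0.5 or 1.0 per SD of lower BHI).

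| Loss depends on | AUC | Observed incidence |
|---|---|---|
| Neither | 0.80 | 10.0% |
| Delirium only | 0.80 | 8.6% |
| Low BHI only | 0.79–0.80 | 8.7–9.4% |
| Both | 0.76–0.78 | 7.1–7.7% |

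Incidence falls whenever delirious patients are lost more often. The AUC moves noticeably only when loss depends on both delirium and BHI. These settings are assumptions, so they show what could happen and do not estimate what will.

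**The case against.** Several stronger readings are tempting, and the documents do not support them.

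- **ICU patients get no postoperative BHI.** A reader might infer this from the ward wording. But Blood Collection says that all patients are sampled twice, and nothing forbids an ICU draw. Wards may simply be the usual place, set against the operating room. What stands is that no other day-1 location is named although ICU patients are in scope.
- **Withdrawal after enrolment is settled.** The exclusion list allows a screening reading, and the Discussion may be describing that criterion loosely. If so, no enrolled patient is lost. What stands is that the two statements differ and the choice matters.
- **A missing day-1 sample removes the patient altogether.** The missing-data sentence does not say this, and the preoperative analysis is affected only if both samples are required. Missing data also include ordinary loss to follow-up, which need not follow illness.
- **The lost patients are known to be the likeliest to become delirious, and the AUC is therefore biased.** The protocol gives no delirium rate for unstable or ICU patients. The link is an inference from its hypothesis, and bias in the AUC is possible rather than shown.

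It is also fair that the Discussion discloses the instability and monocyte exclusions as limitations. Disclosure does not remove a loss that can be avoided cheaply, and it does not cover the ward/ICU gap. Imputation and the handling of deaths or unassessed patients can reasonably be left to an analysis plan and are not part of this point.

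**Conclusion.** The concern holds at moderate severity. The exclusion and withdrawal statements conflict, and the safety reason does not support ending follow-up in a study whose only intervention is venepuncture. The day-1 sampling text leaves ICU patients unclear, so postoperative BHI may be missing for the sickest, and the missing-data rule then drops those values.

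If the lost patients carry 2 to 3 times the risk and make up the planned 10%, 0.9–2.0 events go beyond random dropout. Retained risk is 7.5–8.2% when the true risk is 9%, and 9.2–10.0% when it is 11%. Power across the stated risk range is 85–93%. The power cost is therefore modest. The main damage is to validity: incidence is understated, and the AUC and cutoff may be off if loss also depends on BHI. All of this rests on the assumed null AUC of 0.5, the number lost and their relative risk, none of which the protocol gives for this purpose.

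**What to change.** 1. Reconcile the exclusion list with the Discussion: make instability a pre-enrolment screening criterion. After enrolment it may lead to a study blood draw being omitted, but delirium assessment and 30-day follow-up continue.
2. State that day-1 blood is drawn wherever the patient is, ward or ICU, when the treating team permits.
3. Analyse preoperative BHI in all patients who have it, and postoperative BHI in all patients who have it, so that a missing day-1 value does not remove anyone from the preoperative analysis.
4. Report the number of patients excluded from each analysis, with reasons.

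The cost is revised wording and a few ICU draws by the same team. Outcome follow-up that has been stopped cannot be recovered later.
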